### Data quality assurance

15 days of training for field research assistants and supervisors will be provided. After training on methodological procedures, questionnaires and quality assurance, the questionnaires will be tested in a pilot group and adapted based on the received feedback from the study team. The questionnaires will be translated into the local language (Sidamigna) and back-translated to English to ensure the quality of the translation. Supervisors will receive additional training on teamwork and on monitoring and supervising the data collection process. For laboratory analysis, a quality control chart will be used to ensure the internal and external quality control materials are in the acceptable range.

### Data analysis

#### Empirical approach

Descriptive analysis will focus on computing frequencies and percentages for categorical variables and summary statistics (like means, medians SD, IQR) for summarising continuous variables. To determine the association between dairy consumption and growth outcomes in children 6–18 months of age at the baseline, we will specify a least squares regression model as:

(1)
$$Y_{iv}=\alpha +\beta_{M}M_{iv}+X_{iv}^{\prime }\delta +\varepsilon_{iv}$$

where 
$Y_{iv}$
 is the anthropometric outcome for a child *i* residing in enumeration area *v* measured at various time points. Variable 
$M_{iv}$
 measures the child’s milk intake at various time points. The regression controls for child, parent and household characteristics that are captured in vector 
$X_{iv}$
. These control variables are observable characteristics that are likely to be correlated both with a child’s milk intake and his/her growth outcomes. The terms 
α
 and 
$\varepsilon_{iv}$
 in equation (1) represent the intercept and error term, respectively. The coefficient 
$\beta_{M}$
 quantifies the conditional association between a child’s milk intake and subsequent growth outcome, measured either as HAZ at the end line or as change in HAZ between the baseline and end-line surveys. Considering previous evidence from Ethiopia and elsewhere, we expect 
$\beta_{M}$
 >0.

To determine the association between AFM_1_ levels in milk and nutrient density in milk, we will conduct a univariate analysis on each of the macronutrients and micronutrients and then carryout bivariate tests with AFM_1_ levels in the same samples and determine if and how they are associated with each other.

To determine the association between AFM_1_ exposure and growth outcomes in children 6–36 months of age who consume dairy, we will test whether the consumption of AFM_1_-contaminated milk is associated with lower HAZ (ie, more growth faltering) controlling for confounders and co-factors, including the amount of milk consumed and nutrient content and pathogens in the milk. We will append equation (1) with a variable capturing the child’s AFM_1_ exposure (variable 
$A_{iv}$
). In this model, we also control for the estimated macronutrient and micronutrient content and pathogens (vector 
$C_{iv}^{`}$
) in the milk sample collected at the baseline from the household in which the child resides. We will also control for the child’s maize consumption (vector 
$H_{iv}^{`}$
), since maize is also likely to be contaminated by aflatoxins in the Ethiopian setting.^34–37^ The estimated model can be defined as:

(2)
$$Y_{iv}=\alpha +\beta_{M}M_{iv}+\beta_{A}A_{iv}+\beta_{C}C_{iv}^{\prime }+X_{iv}^{\prime }\delta +H_{iv}^{\prime }\vartheta +\varepsilon_{iv}.$$

We expect that 
$\beta_{A}$
 < 0.

To compare the health benefits versus risks of dairy consumption in child growth outcomes, we will use the regression estimates from equation (2) to conduct joint hypothesis tests for 
$\beta_{M}$
 and 
$\beta_{A}$
, where the null hypothesis is that both of these coefficients are zero, to inform benefit-risk tradeoff of dairy consumption in the context of AFM_1_.

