**Methods and analysis:**

This protocol paper describes our study in Sidama to determine the impact of milk consumption and AFM_1_ on child growth in the first 18 months of life. We will collect baseline and end-line data on dairy production, socioeconomic and nutritional factors of 1000 dairy-owning households with children ages 6–18 months at baseline; and gather samples of milk and dairy feed and child anthropometrics. We will conduct phone interviews every 6 months to ascertain changes in practices or child health. Dairy feed will be tested for AFB_1_; milk for AFM_1_, pathogens and nutrients. Controlling for herd size, socioeconomic, nutritional and behavioural factors, we will determine the association between child anthropometrics and milk consumption, as well as AFM_1_ exposure. We will examine whether AFM_1_ exposure affects child growth in the first 18 months of life, and weigh the benefits and risks of milk consumption.

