### Study setting

The study will be conducted in two districts, Wondo Genet and Hawassa Zuria of Sidama region in Ethiopia (figure 1). These districts are purposely selected due to the common practice of using cow’s milk as complementary food for young children, availability of commercial milk, potential for AFB_1_ contamination in livestock feeds and variation in market access to feed.

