### Sample size calculations

Using the 2016 Ethiopia Demographic Health Survey^22^ and focusing on our primary anthropometric outcome variable, we have mean height-for-age z-scores (HAZ) in children under the age of 36 months of −1.46 (SD=1.56). With the significance level set at 5%, power at 80%, allowing for 10% attrition between survey rounds, and accounting for that not all children consume milk, the study requires approximately 1000 children to detect a 0.3 SD improvement in child HAZ. This minimum detectable effect size corresponds to the estimated association between household cow ownership and child HAZ (children starting at 6–18 months of age) in a study by Hoddinott *et al* in rural Ethiopia.^23^ Since we focus directly on children’s dairy consumption rather than cattle ownership, and our exposure variable is continuous rather than dichotomous, the expected magnitude of the association is likely to be larger than the association documented in Hoddinott *et al*.^23^ Thus, we expect this sample size to offer sufficient precision to detect positive and/or negative associations between AFM1 exposure and growth outcomes in this population.

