### Sampling procedures

Our formative research found that feed ingredients and type varied by herd size and season. Based on these findings, we will classify the dairy cow-owning households into small herd size (one to three cattle) and large herd size (four or more cattle) and randomly select a total of 500 households each from both groups. The two study districts have a list of herd sizes to provide the sampling frame. Within these two groups, all households have an equal chance of being selected.

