#### Estimation methods

The primary outcome variables in most of our statistical models will be continuous and will therefore typically be estimated using the Ordinary Least Squares method. As secondary outcomes, we will also examine dichotomous outcomes—such as stunting or wasting—as dependent variables, in which case we will use both linear probability models and Probit models to implement the regression analysis. Homoscedasticity in the residuals will be tested and if rejected, the SEs will be adjusted for heteroscedasticity following.^38^ All statistical analyses will be conducted using Stata, V.17 or higher.

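### Herd size is sampled on and promised as a control but not named in the models, the rule for choosing controls ignores AFM1, and robust standard errors depend on an unnamed pre-test

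*Protocol article*

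**What the plan says.** All references are to the protocol article.

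- **Abstract, Methods and analysis.** The associations of growth with milk consumption and with AFM1 exposure are to be estimated "Controlling for herd size, socioeconomic, nutritional and behavioural factors".
- **Sampling procedures.** Formative work found that feed differs by herd size and season. Households are split into small herds (one to three cattle) and large herds (four or more), and the team will "randomly select a total of 500 households each from both groups".
- **Study setting.** One reason for choosing the two districts was "variation in market access to feed".
- **Control variables.** The examples given are the child's sex, age and diet, parental education, a wealth index, milk nutrients, milk pathogens and maize consumption. Herd size, district and sampling date are not among them.
- **Empirical approach.** X in equation (1) holds child, parent and household characteristics, chosen by this rule: "These control variables are observable characteristics that are likely to be correlated both with a child’s milk intake and his/her growth outcomes". Equation (2) keeps the same X and adds AFM1 exposure, milk composition and pathogens, and maize consumption.
- **Estimation methods.** "Homoscedasticity in the residuals will be tested and if rejected, the SEs will be adjusted for heteroscedasticity". No test is named. The same section specifies linear probability models, alongside Probit, for stunting, wasting and similar outcomes.

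**The concern.** The AFM1 coefficient, beta_A, is the parameter the study exists to estimate. The design is observational, and the Discussion relies on adjustment for observed confounders to limit bias. A confounder of beta_A is a variable related to AFM1 and to growth. The stated rule selects on milk intake and growth instead, so a variable that drives contamination but not the amount of milk drunk would not meet it. The document points to such candidates itself: herd size, season and local feed-market access.

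The direction of any bias matters. If large-herd households had both more contaminated milk and better-growing children, omitting herd size would push beta_A upward, against the expected negative sign, and could hide harm. The reverse pattern would exaggerate harm.

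The standard-error rule is a separate matter. Passing a homoscedasticity test does not establish constant variance, and in a linear probability model the variance changes with the fitted probability. The error rate of every test then depends partly on which pre-test happens to be run.

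**Working it through.** The plan gives no figure for either issue, so there is none to reproduce. The point does not turn on the target of 1000 children.

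**1. Where herd size, season and district appear**

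| Place | Herd size | Season or date | District |
|---|---|---|---|
| Abstract | promised as control | no | no |
| Sampling procedures | stratum | noted as affecting feed, not sampled on | source of the list only |
| Control variables | not named | phone data used to assess seasonality and adjust for consumption variability | not named |
| Equations (1) and (2) | not named | no term | no term |

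**2. Possible bias in beta_A if herd size is left out**

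Inputs from the document:
- HAZ SD 1.56 ("in children under the age of 36 months of −1.46 (SD=1.56").
- 1000 children less 10% attrition = 900 ("With the significance level set at 5%, power at 80%, allowing for 10% attrition between survey rounds").
- Stratum share p = 0.5, from the 500/500 split, so p(1−p) = 0.25.

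Assumed inputs, not in the document:
- g, the HAZ difference between strata that remains after the other controls.
- d, the AFM1 difference between strata in within-stratum SDs.

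Bias = g × d × 0.25 / (1 + 0.25 d²). The rough SE of beta_A is 1.56/√900 = 0.052.

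| g | d | Bias (HAZ per SD of AFM1) | Bias/SE | Actual size of a 5% test |
|---|---|---|---|---|
| 0.1 | 0.2 | 0.005/1.01 = 0.005 | 0.10 | 5.1% |
| 0.3 | 0.5 | 0.0375/1.0625 = 0.035 | 0.68 | 10.4% |
| 0.5 | 0.8 | 0.100/1.16 = 0.086 | 1.66 | 38% |

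The last column is 1 − Φ(1.96 − t) + Φ(−1.96 − t), with t = bias/SE. Restricting the AFM1 model to milk consumers would lower n, raise the SE and so reduce the ratio.

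**3. The pre-test rule**

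In a linear probability model Var(Y|x) = p(x){1 − p(x)}. As an illustration, fitted probabilities of 0.1 and 0.5 give variances of 0.09 and 0.25. Constant variance fails whenever the fitted probability varies.

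For a continuous outcome the rule was simulated under the null with n = 450, 4000 runs, error SD = exp(g|x|) with x standard normal (here g is only the strength of the variance pattern), and a nominal 5% test:

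| Rule | g = 0.1 | g = 0.2 | g = 0.3 |
|---|---|---|---|
| Breusch-Pagan pre-test | 6.3% | 8.9% | 10.2% |
| White pre-test | 5.4% | 5.4% | 4.9% |
| HC3 always | 4.6% | 5.2% | 4.9% |

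Repeat runs at n = 450 and n = 900 gave about 7–11%, 4–7% and 4–6% for the three rules.

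A second assumed pattern had a skewed exposure, variance rising in one direction and n = 900. There the pre-test rule gave 5.1–7.8%, always-robust (HC1) 6.1–7.7%, and never-robust up to 28%. In that pattern the pre-test did almost no harm.

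**The case against.** The strongest reply is that nothing is actually excluded. The abstract commits to herd size, the Methods list is open, X is defined to include household characteristics, and the text before equation (2) speaks of confounders and co-factors in open terms. A condensed article may leave the full covariate list to another document. Wealth, parental education and diet are controlled and may absorb much of any herd-size effect. Whether AFM1 differs by feedstuff is itself something the study sets out to learn. All of this stands, and it is why bias is a risk here and not a demonstrated result. It does not answer the written selection rule, which refers to the wrong exposure for equation (2), or the mismatch between abstract and Methods.

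On standard errors, the reply is that a White-type pre-test controls error about as well as HC3, that the linear probability models serve secondary outcomes, and that Probit is run beside them. That also stands. But the plan does not name the test, and its error control depends on that choice.

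A reader might also go further than the document allows:

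- **That season was a sampling factor.** It was not; only herd size was.
- **That unweighted AFM1 means from the 500/500 sample would mislead against the 0.5 µg/L limit.** The document gives neither the frame share nor the AFM1 mean of either stratum. The 0.41 and 0.69 µg/L in the Introduction bound a range of means from earlier raw-milk samples and are not stratum values. The analytic objectives are associations, for which an unweighted regression with the stratum in the model can be valid. Weights of listed households divided by 500 could themselves be wrong, because eligibility also needs a child aged 6–18 months.

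**Conclusion.** The point holds in two parts.

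First, the abstract and the Methods disagree on herd size, and the confounder rule is not written for AFM1, although the plan itself links feed to herd size and season and chose its districts for feed-market variation. The resulting bias in beta_A could be negligible (0.005 HAZ per SD of AFM1) or material (about 0.09). The range rests entirely on assumed differences between strata. To say that the AFM1 results will be confounded would claim more than the document supports.

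Second, the conditional robust-SE rule is unsound for linear probability models and leaves type I error for continuous outcomes dependent on an unnamed test: about 5% to 11% under the |x| variance pattern, and little different from always-robust under the other. A reader might infer that the study's standard errors are unreliable in general. The simulations do not show that.

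Both parts should be corrected. Neither invalidates the design.

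**What to change.** 1. In the Control variables and Empirical approach sections, name herd-size stratum, district and month of milk sampling as elements of X in equations (1) and (2).
2. Extend the selection rule so that, for equation (2), X also includes variables likely to be related to AFM1 and to growth.
3. In Estimation methods, delete the homoscedasticity pre-test and state that heteroscedasticity-robust standard errors (for example HC3) are used in every OLS and linear probability model.
4. Optionally, report descriptive AFM1 summaries by herd-size stratum. No weighting is asked for.

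Herd size and district are known from the sampling frame, and the month of milk sampling needs only the visit date, so this is mainly a change of wording. It costs one degree of freedom each for stratum and district, plus one fewer than the number of sampling months. Adjusting for herd size also removes some AFM1 variation. If the strata differ by d within-stratum SDs, the SE of beta_A rises by a factor of √(1 + 0.25 d²), that is √1.0625 = 1.03 for d = 0.5 and √1.16 = 1.08 for d = 0.8, before any gain from explaining HAZ.

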### Outcome variables

Anthropometric status indicators are the main outcome variables for this study. Anthropometric measurements—weight, height/length, mid-upper arm circumference (MUAC) and head circumference—will be collected from the children at baseline and end line. Height/length will be measured using height/length boards, with the measurements recorded to the nearest 0.1 cm. Weight will be measured using a digital weighing scale (Seca 874 digital floor scale) and recorded to the nearest 0.1 kg. Head circumference will be measured by using a Seca paediatric head circumference measuring band to the nearest 0.1 cm decimal.

Using the WHO 2006 child growth standards, we will calculate HAZ, weight-for-height z-scores (WLZ), weight-for-age z-scores (WAZ) and head circumference-for-age z-scores (HCZ). The HAZ is the primary variable of interest and as secondary outcomes, we will consider the dichotomous variable of stunting (ie, HAZ below −2 SD), WLZ and wasting (ie, WLZ below −2 SD), WAZ and underweight (ie, WAZ below −2 SD), MUAC and HCZ.

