### Control variables

Data on the control variables will be collected during the survey visits and will include characteristics that are likely to be correlated with child growth outcomes and child’s milk intake. This includes variables such child’s sex, age and diet, parent’s education, household wealth index, milk’s nutrient content, pathogens in milk and child’s maize consumption.

A questionnaire will collect information about child, parent and household characteristics. Information on children’s diet comes from the 24-hour recall survey. We will control for children’s diets by calculating caloric intake variables from eight food groups: (1) Breastmilk, (2) Grains, roots and tubers, (3) Pulses, nuts and seeds, (4) Dairy products, (5) Flesh foods (meats, fish, poultry, organ meats), (6) Eggs, (7) Vitamin-A rich fruits and vegetables and (8) other fruits and vegetables.^26^ Additionally, we will collect detailed data on the non-standard recipe’s ingredients for all mixed dishes that were prepared at home and use standard recipes from the National Food and Nutrition baseline survey dietary data set to assess the amount of food consumed.^27^ The dietary surveys will be administered outside of major Ethiopian Orthodox fasting periods during which dairy household availability and consumption may decline sharply.^28^

One potential source of measurement error in linking food consumption to child growth is within-person variability in consumption. Since linear growth in young children depends on long-term dietary quantity and quality, the 24-hour recall method is imperfect for capturing variability in diets over time.^29^ To address this, we will conduct interim phone surveys every 6 months to ask caregivers about the 24-hour milk consumption and weekly recall of the child’s diet diversity, and assess basic milk production. These higher frequency measurements will be used to assess seasonality, variability, and to adjust for consumption variability in our analysis.

A subsample of 500 livestock feed samples will be collected for testing AFB_1_. Detection of AFB_1_ in feed samples will be achieved using the Helica Low Matrix Aflatoxin B_1_ competitive ELISA kit, manufactured by Helica Biosystems, Santa Ana, California, USA, listed under Catalogue Number 981BAFL01LM-96 and using procedures outlined by them.^30^

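### The primary outcome is left as either end-line HAZ or change in HAZ, unranked, and the written models carry no baseline HAZ term although baseline HAZ is collected

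*Protocol article*

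**What the plan says.** Under Outcome variables, the article states "The HAZ is the primary variable of interest and as secondary outcomes" lists the others, but it fixes neither a time point nor a form for HAZ. The same section says that the anthropometric measurements "will be collected from the children at baseline and end line".

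Under Empirical approach, the outcome in equation (1) is "measured at various time points", and milk intake is described in the same way; the equation has no time subscript. The milk coefficient is then tied to later growth, "measured either as HAZ at the end line or as change in HAZ between the baseline and end-line surveys". Neither form is ranked above the other.

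On covariates: "The regression controls for child, parent and household characteristics that are captured in vector" X. The Control variables section names "variables such child’s sex, age and diet, parent’s education, household wealth index" and goes on to milk nutrients, pathogens and maize. Baseline HAZ is not named. Equation (2) appends AFM1 exposure, milk composition and pathogens, and maize intake to equation (1); it adds no baseline outcome term.

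**The concern.** The Objectives ask about growth impairment over 18 months, and equation (1) is read as a statement about growth after exposure is measured. Children enter at 6–18 months with their height deficit partly formed. End-line HAZ with no baseline term adds that earlier growth to the growth of interest. It also picks up any tendency of caregivers to give more or less milk to children who are already small.

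Change in HAZ removes the starting level by subtraction, but it answers the question under a different assumption about confounding. The two outcomes can therefore disagree, and the article gives no rule for which one counts. Because equation (2) is built from equation (1), the AFM1 coefficient and the joint benefit-risk test inherit the open choice. The article states expected signs for both coefficients, so an unranked choice leaves room to prefer the version that agrees with them. These estimates are meant to inform regulation of AFM1 in milk.

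**Working it through.** **Inputs.** The SD of HAZ is 1.56, from Sample size calculations ("in children under the age of 36 months of −1.46 (SD=1.56"). The same section gives 5% significance (two-sided assumed), 80% power, about 1000 children and 10% attrition, so 1000 × 0.9 = 900 completers. The article does not give *r*, the correlation between baseline and end-line HAZ, or *ρ*, the correlation between milk intake and baseline HAZ. Both are assumed below.

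**1. The plan's own sample size.** Per group, n = 2 × [(1.960 + 0.842) × SD / difference]².
- Difference of 0.3 SD: 175 per group, 350 in total, 350/0.9 = 389.
- Difference of 0.3 HAZ units with SD 1.56: 425 per group, 850 in total, 850/0.9 = 945.

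A figure near 1000 appears only with an assumed share of milk drinkers. At 40% it is 350/(0.4 × 0.9) = 972 for 0.3 SD in drinkers only, or 983 for 0.3 HAZ in drinkers against non-drinkers. The article gives no share, so its figure is neither confirmed nor refuted, and this point does not depend on it. The SD used is cross-sectional, with no allowance for *r*.

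**2. Precision.** Relative residual variance, before other covariates, is 1 for end-line HAZ, 2(1 − r) for change and 1 − r² for end-line HAZ adjusted for baseline. The minimum detectable difference with 900 completers split 1:1 is 2.802 × 1.56 × √(4/900) = 0.291 HAZ for end-line HAZ, and scales with the square root of the variance.

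| r | Variance: end-line / change / adjusted | Detectable difference (HAZ) |
|---|---|---|
| 0.3 | 1 / 1.40 / 0.91 | 0.291 / 0.345 / 0.278 |
| 0.5 | 1 / 1.00 / 0.75 | 0.291 / 0.291 / 0.252 |
| 0.6 | 1 / 0.80 / 0.64 | 0.291 / 0.261 / 0.233 |
| 0.7 | 1 / 0.60 / 0.51 | 0.291 / 0.226 / 0.208 |
| 0.8 | 1 / 0.40 / 0.36 | 0.291 / 0.184 / 0.175 |

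For r of 0.5–0.7, end-line HAZ needs 1/0.75 = 1.33 to 1/0.51 = 1.96 times as many children as the adjusted model. Change needs 1.00/0.75 = 1.33 to 0.60/0.51 = 1.18 times as many.

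**3. Sign and bias with no true effect of milk.** Take r = 0.6 and ρ = +0.1. Slopes are in HAZ per SD of milk intake.

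*Structure A: milk is related to end-line HAZ only through measured baseline HAZ.*
- End-line: 1.56 × 0.6 × 0.1 = +0.094.
- Change: 1.56 × (0.6 − 1) × 0.1 = −0.062.
- Adjusted: 0.

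Simulation with n = 900 gave +0.095, −0.062 and 0.00, with false rejections of 45%, 27% and 5%. With ρ = −0.1 the two non-zero signs reverse.

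*Structure B: a stable unmeasured factor raises HAZ equally at both visits and is related to milk.*
- End-line: 1.56 × 0.1 = +0.156.
- Change: 0.
- Adjusted: 1.56 × 0.1 × (1 − 0.6)/(1 − 0.1²) = +0.063.

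Simulation gave change 0.00 (5% false rejections) and adjusted +0.063 (33%).

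Baseline adjustment is closer to zero than unadjusted end-line HAZ under both structures (0.00 against 0.09; 0.06 against 0.16). Change is worse than adjustment under A and better under B.

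**4. Two chances.** With no effect and ρ = 0, the end-line and change estimates correlate at √((1 − r)/2), which is 0.50 at r = 0.5 and 0.39 at r = 0.7. Testing each at 5% and claiming either gives about a 9% chance of at least one false positive per coefficient.

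**The case against.** The strongest objection is that exposure is not randomised, so no general result favours baseline adjustment over change. Under structure B change is unbiased and adjustment is not, and the Discussion says that only observable confounders are controlled. Error in measuring infant length would also leave residual bias after adjustment. This stands. A reader might infer that change in HAZ is a biased outcome; the article does not support that as a general claim. The objection does not rescue an unranked choice, nor end-line HAZ without a baseline term, which does worse than adjustment under both structures.

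The covariate list is open and an article need not give it in full, so baseline HAZ might be meant to enter X. A reader might infer that it has been excluded; the text says only that it is not in the written models or among the named controls. The outcome itself, however, is written out as an either/or, and that is not a detail left to another document.

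A reader might call the end-line version cross-sectional. It is not: milk intake is related to a later outcome, with end line 18 months after the first visit. Attained height is a legitimate target, but it is a different one from later growth. Change is likewise not blind to baseline, since it subtracts it.

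The article does not say that both forms will be tested and either claimed, so the 9% is conditional. The sentence with the choice concerns the milk coefficient only; for AFM1 the text speaks of lower HAZ, and the ambiguity comes through equation (1). The precision gain would also shrink where age, sex, diet, education and wealth already explain part of the stability of HAZ.

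**Conclusion.** The point holds in this form: the primary form of HAZ is not fixed, and the written models omit a baseline value that the study collects and that its question about later growth calls for. Unadjusted end-line HAZ costs 33–96% more children than the adjusted model for r of 0.5–0.7, before other covariates; the adjusted model has the smallest residual variance at any r strictly between 0 and 1. The two permitted outcomes can differ in sign (+0.09 against −0.06 HAZ per SD of milk under structure A with r = 0.6 and ρ = 0.1).

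All these sizes rest on correlations that the article does not give. Which analysis is less biased, adjustment or change, depends on a causal structure that the data cannot settle. The point is worth correcting before analysis; it does not invalidate the design.

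**What to change.** Name one primary model and use it for equations (1) and (2), one row per child: end-line HAZ regressed on exposure, with baseline HAZ, age at both visits and sex as covariates alongside the planned controls. Add time subscripts to the equations.

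Pre-specify change in HAZ as a sensitivity analysis, state that it rests on stable unmeasured confounding, and say in advance that a disagreement between the two will be read as a sign of confounding, not as a choice of result. Do the same for the other continuous outcomes (WAZ, WLZ, MUAC and HCZ).

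The cost is wording, since the baseline measurements are already planned. The downside is small but should be stated: the estimate concerns growth after enrolment and leaves out any effect of milk or AFM1 already present at baseline.
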